**Enrolment**									
Informed consent PRESENT cohort	X								
Eligibility screening BLEND RCT	X								
Randomization BLEND RCT	X								
Informed consent BLEND RCT (upon acceptance of intervention)		X							
**Interventions**									
BLEND procedure		X (same-day RT and surgery)							
Standard of care		X (surgery followed by RT when the wound healed sufficiently, usually > 1 week)							
**Assessment**									
PROMs used for BLEND RCT effect estimation primary outcome					X				
PROMs used for BLEND RCT effect estimation secondary outcome			X	X	X	X	X	X	X

#### Sample size {14}

Four weeks after the start of treatment, patients in the control group may just have received radiotherapy or still need to undergo radiotherapy. Therefore, we assume that they do not experience a pain response yet at that time point. From the PRESENT cohort, we know that patients who did not experience a pain response after radiotherapy had a physical functioning mean score of 43.6, 4 weeks after the start of radiotherapy.

A recent study reported a minimal clinically important difference (MCID) of 13 points on the EORTC QLQ-C15-PAL physical functioning scale in patients with bone metastases undergoing radiotherapy [22]. To detect a 13 point difference with an 80% power, a two-sided *α* of 5% and standard deviation of 22, 45 patients are needed in each arm. We expect that 90% of the patients offered the intervention will accept the offer. To compensate for refusal, questionnaire nonresponse, and possible dropouts, we will increase the sample size by 10%, resulting in a total sample size of 100 patients.

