#### Interim analyses {21b}

An interim analysis will be performed when 50% of the patients have been randomized and completed the 4 weeks follow-up period. This analysis will be performed to assess how many patients complete the primary outcome measurement and to estimate the drop-out rate. If the drop-out rate is higher than expected (i.e., > 10%), we should consider to update the sample size to prevent an underpowered study [29].

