#### Methods in analysis to handle protocol non-adherence and any statistical methods to handle missing data {20c}

Analysis will be based on the intention-to-treat principle. However, in accordance with the TwiCs design, patients who are selected for the intervention arm may refuse the intervention. In case of a high refusal rate (i.e., > 15%), we will also conduct a per protocol (PP) analysis including patients who completed the treatment as allocated. However, refusal may be selective, e.g., patients who are less physically fit may refuse the intervention. As a result, PP analysis may under- or overestimate the treatment effect. We will also perform a complier average causal effect (CACE) analysis to estimate the treatment effect among “compliers,” i.e., patients that accepted and received the intervention offered compared with hypothetical control patients who, if offered the intervention, would have accepted.

In the palliative oncology setting, questionnaire non-response is more likely due to inability to complete questionnaires as a result of for example fatigue and high distress or filling in questionnaires may be too burdensome. The proportion and patterns of missing data for the primary and secondary outcomes will be investigated. If needed, multiple imputation methods will be used to handle missing data under the assumption that data is missing at random. If the primary outcome data is determined to be missing not at random, a best–worst and worst-best case sensitivity analyses will be performed.

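### The sample size treats expected refusal as lost observations, although refusers stay in the intention-to-treat analysis and dilute the effect; one 10% inflation does not cover both refusal and missing data

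*Protocol article*

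**What the plan says.** Sample size {14} of the Protocol article takes its target from a published minimal clinically important difference: "A recent study reported a minimal clinically important difference (MCID) of 13 points on the EORTC QLQ-C15-PAL physical functioning scale". It continues: "To detect a 13 point difference with an 80% power, a two-sided *α* of 5" per cent, and "standard deviation of 22, 45 patients are needed in each arm". On uptake it says: "We expect that 90% of the patients offered the intervention will accept the offer". One allowance then covers three different losses: "To compensate for refusal, questionnaire nonresponse, and possible dropouts, we will increase the sample size by 10" per cent, which brings the total to 100.

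Three other sections decide what refusal does to the primary comparison.

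- Intervention description {11a} gives patients who refuse the same standard of care as the control arm.
- Statistical methods {20a} plans linear regression or ANCOVA by intention-to-treat, adjusting for baseline physical functioning, age, Karnofsky score and medication use.
- The section on non-adherence and missing data {20c} repeats the principle: "Analysis will be based on the intention-to-treat principle". It adds a per-protocol analysis if refusal exceeds 15%, and a complier average causal effect (CACE) analysis.

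Interim analyses {21b} checks completion of the primary outcome and drop-out at the halfway point: "If the drop-out rate is higher than expected (i.e., > 10%), we should consider to update the sample size". Refusal is not mentioned there.

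**The concern.** Missing outcomes and refusal act on power in different ways. A missing outcome removes an observation, and dividing the required number by the retained fraction corrects for it. A refuser analysed by intention-to-treat still contributes an observation, but one made under the control treatment. That pulls the arm means together, and the required number rises with the inverse square of the acceptance rate. Sample size {14} applies the first correction to both.

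The same 10% also has to cover non-response and drop-out. Interim analyses {21b} treats drop-out of up to 10% as expected, and that alone takes 50 per arm back to 45. Nothing is then left for refusal.

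At stake is the stated type II error of the primary test. If the true risk of missing a worthwhile effect is nearer 30% than 20%, an inconclusive result is easier to misread as absence of benefit.

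**Working it through.** **Inputs.** From Sample size {14}: difference 13, SD 22, two-sided 5%, power 80%, acceptance 90%, total 100 (50 per arm at 1:1). From Interim analyses {21b}: drop-out up to 10% treated as expected. From Intervention description {11a}: refusers receive standard of care.

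**1. Reproduce the plan's figure.** n per arm = 2(1.96 + 0.8416)² × 22² / 13² = 44.96, so 45. Allowing for 10% loss: 45/0.9 = 50 per arm, 100 in total. Both stated numbers reproduce. Power at 45 per arm and 13 points is 80.0% by the normal formula and 79.2% by the t-test, so just under one point of any gap from 80% in the t-test figures below is due to the method.

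**2. Dilution.** If acceptors gain 13 points and refusers gain nothing, the intention-to-treat contrast is 0.9 × 13 + 0.1 × 0 = 11.7 points. Mixing the two groups raises the intervention-arm SD only to √(22² + 0.9 × 0.1 × 13²) = 22.3, which is ignored here.

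**3. Inflation needed for refusal alone.** (13/11.7)² = 1/0.9² = 1.235. The required number is 2(1.96 + 0.8416)² × 22² / 11.7² = 55.5, so 56 per arm (57 by the t-test). The plan's step from 45 to 50 is a factor of 1.11.

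**4. Power with 100 randomised, unadjusted, SD 22.** Normal formula: Φ(d/22 × √(n/2) − 1.96).

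| Analysable per arm | Difference | Normal | t-test |
|---|---|---|---|
| 50 (none missing) | 11.7 | 75.8% | 75.0% |
| 45 (10% missing) | 11.7 | 71.3% | 70.4% |
| 50 (none missing) | 13 | 84.0% | 83.3% |
| 45 (10% missing) | 13 | 80.0% | 79.2% |

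The last two rows apply if 13 points is itself the intention-to-treat target. The implied effect among acceptors is then 13/0.9 = 14.4 points.

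**5. What covariate adjustment would have to supply.** Replacing the SD by 22√(1 − r²), where r is the correlation between the covariates taken together and the outcome, 80% power at 11.7 points needs:

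- 50 per arm: r = 0.31 (normal) or 0.34 (t-test), so about 0.35 to be safe;
- 45 per arm: r = 0.43 (normal) or 0.455 (t-test), so about 0.46.

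The document gives no value for r.

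**6. Interim rule.** With 10% refusal and 10% drop-out together, the drop-out rate does not exceed 10%, so the rule is not met. The unadjusted power in that case is the 70–71% of the second row.

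**The case against.** The strongest reply is that 13 points may be the intention-to-treat difference. It is introduced as a minimal important difference, not as the expected effect among acceptors, and the primary comparison is by intention-to-treat. On that reading, 45 analysable per arm gives about 80% and 100 patients cover 10% missing data. This is a fair reading, but it does not rescue the paragraph. Refusal would then need no compensation, yet it is the first loss named. Whichever reading is meant, the text needs correcting.

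The second reply is that the trial will not run an unadjusted test. The planned model has four covariates, and a moderate joint correlation would restore 80%. This stands as a limit on the point. A reader might infer that the trial is simply underpowered. The document does not support so flat a statement, because the shortfall is shown only for the calculation as written. Equally, the sample-size section claims no credit for adjustment and states no correlation.

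A reader might also work through harsher scenarios, such as 20% missing or 15% refusal. Neither is an expectation of the plan. The 10% drop-out figure is a trigger, and {11c} and {18b} provide telephone follow-up to limit missing primary outcomes.

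Nor is it right that nothing in the plan deals with dilution. The CACE analysis in {20c} estimates the effect among those who would accept, which helps guard against misreading a diluted null result. It does not restore the power of the primary test.

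**Conclusion.** The point holds in this form. Sample size {14} corrects for refusal as if it were missing data, and uses a single 10% both for refusal and for the drop-out that Interim analyses {21b} already treats as expected. On the plan's own unadjusted basis, the stated 80% becomes about 75–76% with complete data and about 70–71% with 10% missing.

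These figures assume that 13 points is the effect among acceptors, that refusers gain nothing, and that refusers do not differ in prognosis. The stated 45 and 100 are computed correctly from their inputs, so the fault lies in the assumption about what refusal does. Whether the planned ANCOVA makes up the difference cannot be settled from the document. Severity: should be fixed. It changes a stated operating characteristic, but not the design, the primary outcome or the analysis.

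**What to change.** State in Sample size {14} which effect the 13 points describes.

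- **If it is the intention-to-treat difference:** remove refusal from the list of losses, reserve the 10% for missing outcomes (45 analysable per arm, about 80% power), and say that at 90% acceptance this implies about 14.4 points among acceptors.
- **If it is the effect among acceptors:** give the intention-to-treat target as 11.7 points and restate power with 100 patients as about 70–75%. Alternatively, keep 80% and state the covariate–outcome correlation in the planned ANCOVA on which it rests: about 0.35 with no missing data, about 0.46 with 10% missing.

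In Interim analyses {21b}, have the check consider observed refusal alongside drop-out, since 10% of each together would not prompt a review. A fuller re-estimation, for example from the residual SD, would be a design preference and is not needed to correct the error.

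The cost is rewording two paragraphs. No extra patients are needed; the stated power becomes either lower or conditional on a stated assumption.

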### Recruitment {15}

For this study, no recruitment strategies will be used as eligible patients will be identified from the PRESENT cohort.

### Assignment of interventions: allocation

#### Sequence generation {16a}

A computer-generated allocation sequence will be created using random permuted blocks of patients. Randomization will be stratified by spinal metastases from renal cell carcinoma versus other histologies.

#### Concealment mechanism {16b}

Patients will be randomized using Castor (Amsterdam, The Netherlands, www.castoredc.com), an electronic data capture system. Allocation concealment will be ensured as Castor will not release the randomization code until the patient has been recruited into the trial.

#### Implementation {16c}

The research team will screen patients on eligibility. If a patient appears eligible, the research team will perform online randomized allocation.

### Assignment of interventions: blinding

#### Who will be blinded {17a}

Patients randomized to the control group will not be informed about the trial and receive standard of care. Hence, patients in the control group will be blinded to group allocation. They will even be unaware of the existence of this trial. In contrast, patients randomized to the intervention group will be informed about the intervention which they can accept or refuse. It is not possible to blind researchers and clinicians for group allocation.

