#### Data management {19}

Demographic and clinical data will be collected in the electronic data capture system Castor (Amsterdam, The Netherlands, www.castoredc.com). The database includes multiple build-in skips and data validation checks to promote data quality, and an electronic audit trial log of all study event is stored. The data will be managed by a data manager and the research team will have access to the data. Access will be managed by authorization of accounts. PROMs will be sent out to the patients using PROFILES, which stands for Patient Reported Outcomes Following Initial treatment and Long term Evaluation of Survivorship (www.profielstudie.nl). Patients can complete the questionnaire on paper or online. Hardcopy questionnaires will be entered into PROFILES and physically stored in a secure archive of the study site. For other study files, a local secured research folder on the network drives of the study site will be used to be sure that only authorized personnel have access to the data.

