### Statistical methods

#### Statistical methods for primary and secondary outcomes {20a}

The primary outcome is physical functioning 4 weeks after the start of the treatment, which will be expressed as a score on a 0–100 scale. First, we will calculate within-group changes from baseline to 4 weeks after the start of the treatment, which will be expressed as mean changes with corresponding 95% confidence intervals. Linear regression analysis or analysis of covariance (ANCOVA) following the intention-to-treat principle will be performed to compare the intervention arm with the control arm in terms of physical functioning, controlling for baseline physical functioning, age, Karnofsky performance score, and medication use. Differences between treatments and 95% confidence intervals will be calculated.

The proportion of patients in the intervention and control arm reporting a pain response will be compared by Fisher’s exact test or *χ*^2^ test.

Within-group changes in HRQOL from baseline to 4 and 8 weeks and 3 and 6 months will be expressed as mean change with corresponding 95% confidence intervals. We will assess between-group differences in HRQOL as a continuous outcome using linear regression analysis. The proportion of patients with a clinically relevant improvement or deterioration, i.e., an increase or decrease, respectively, of at least 10 points will be compared between the intervention and control arm at every time point by Fisher’s exact test or *χ*^2^ test [24, 28]. In addition, the proportion of patients reporting a clinically relevant improvement at any time point within 3 months will be compared.

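### Section {17a} says too broadly that researchers cannot be blinded: whoever runs the primary intention-to-treat analysis could work on coded arms

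*Protocol article*

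**What the plan says.** Section {17a} explains that control patients do not know of the trial and that intervention patients do, and then closes with "It is not possible to blind researchers and clinicians for group allocation". No exception is made for the analyst, and the article nowhere mentions coded arms or a masked analysis.

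Two other sections show what the research team knows. Section {16c}: "If a patient appears eligible, the research team will perform online randomized allocation". Section {19}: "The data will be managed by a data manager and the research team will have access to the data".

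The primary analysis is in section {20a}: "Linear regression analysis or analysis of covariance (ANCOVA) following the intention-to-treat principle will be performed", adjusted for baseline physical functioning, age, Karnofsky score and medication use.

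Section {20c} covers missing data: "If needed, multiple imputation methods will be used to handle missing data under the assumption that data is missing at random". It continues: "If the primary outcome data is determined to be missing not at random, a best–worst and worst-best case sensitivity analyses will be performed". No criterion is given for either condition. The same section does give a numeric trigger for the per-protocol analysis (refusal above 15%).

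**The concern.** An open-label procedure rules out masking the surgeon, the radiation oncologist and the person who makes the offer. It does not rule out masking the person who fits a regression to a 0–100 questionnaire score. By calling blinding of researchers impossible, the article gives up a protection that is available.

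That protection has some value here. The trial has one centre, the primary endpoint is subjective, and the abstract says the investigators expect better functional outcomes with same-day treatment. Section {20c} itself expects non-response from fatigue and distress, so the question of imputation is likely to arise. If it is answered by someone who knows the arms and has seen the comparison, a positive result is easier to challenge.

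**Working it through.** The claim is about the reach of a sentence, so most of the check sets sections side by side.

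**1. The plan's own figure.** With a difference of 13, SD 22, two-sided 5% and 80% power (section {14}), n per arm = 2 × (1.960 + 0.842)² × 22² / 13² = 2 × 7.85 × 484 / 169 ≈ 44.96, so 45. Allowing for 10% loss, 45 / 0.90 = 50 per arm, 100 in total. The plan's figure reproduces, and masking the analyst does not change it.

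**2. What the primary model needs, and whether it reveals the arm.**

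| Item | Source | Reveals the arm? |
|---|---|---|
| Arm | {20a} | No, if coded A/B |
| 4-week physical functioning | {12}, {20a} | No |
| Baseline functioning, age, Karnofsky score, medication use | {20a} | No, taking all as pre-treatment values (an assumption for the last two) |
| Acceptance or refusal | {20c} | Yes: only the intervention arm is offered anything; needed for per-protocol and complier average causal effect (CACE) analyses, not for the primary model |
| Dates of surgery and radiotherapy | {11a}, {12} | Yes: the order differs by arm; not a model term, but needed to check the 4-week window |
| Exclusion after randomization, e.g. when radiation planning fails | {11b} | It may; bears on the analysis set |

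The model can therefore be run masked. The analysis set cannot be settled wholly masked, because section {11b} exclusions and the start-of-treatment anchor in section {12} can point to the arm.

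**3. Who is placed around the analysis.** The research team randomizes ({16c}), has access to the data ({19}) and is described as unblindable ({17a}). No section says who runs the analysis or decides on imputation. That this person is unmasked is an inference from these three sections.

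**4. Which open choices can move the primary result.**

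- Imputation when needed: yes. Complete-case and imputed estimates can differ.
- Judging data to be missing not at random: no. This only adds sensitivity analyses, run in both directions.
- Fisher or χ²: no. This applies to secondary proportions.
- Linear regression or ANCOVA: no. With these covariates they are in effect one model.
- Per-protocol analysis: no. It is an additional analysis with a numeric trigger.

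One choice remains.

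**5. Does masking alone stop a favourable pick?** Suppose two analyses of the primary outcome have null test statistics with correlation ρ (assumed). The chance that at least one is significant at two-sided 5% is 1 − P(|Z₁| < 1.96, |Z₂| < 1.96). In the favoured direction alone it is 1 − P(Z₁ < 1.96, Z₂ < 1.96), against 2.5% for a single test.

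| ρ | Two-sided | Favoured direction |
|---|---|---|
| 0.80 | 7.8% | 3.9% |
| 0.90 | 7.0% | 3.5% |
| 0.95 | 6.5% | 3.2% |

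The last column is half of the middle one. A masked analyst who simply takes the smaller two-sided p-value therefore errs in the favoured direction as often as an unmasked one, because swapping the labels leaves a two-sided p-value unchanged. The excess comes from the open imputation rule. Coding the arms would not lower it, but deciding on imputation before any comparison would.

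**The case against.** The strongest reply is that analyst masking, coded arms and imputation triggers usually belong in an SAP or full protocol, neither of which is shown. Their absence from an article is then no defect. This is right for the missing detail. It does not rescue the sentence in section {17a}, which asserts an impossibility; an SAP that masked the analyst would contradict it.

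A reader might infer that the protocol has people who know the arms make the analysis choices. It does not say so. It names no analyst, and the sections in step 3 support only a natural reading.

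A reader might also count "If the primary outcome data is determined to be missing not at random" and the choice between Fisher and χ² as freedom over the primary result. They are not: the first leads to sensitivity analyses in both directions, and the second concerns secondary outcomes.

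Two further objections stand. The outcome is patient-reported, so masking the analyst does not affect how scores arise. Sections {11c} and {18b} have research staff telephone non-responders for their primary-outcome answers, and those staff may know the arm. That is a more direct route to bias, and this change leaves it untouched. Also, masking the whole analysis set is not feasible (step 2), so part of that work must be done beforehand by someone who can see revealing data.

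**Conclusion.** The concern holds in a limited form. The statement on blinding is true of clinicians and of staff who allocate or offer treatment, and too broad for the primary analyst. Together with imputation left to "If needed, multiple imputation methods will be used to handle missing data", it leaves one avoidable opening on the primary result. This is a minor improvement worth making because it is cheap; it is not a flaw that undermines the trial.

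The documents give no basis for putting a number on the harm. A reader might take an error rate of about 6–7% as the price of not masking. Step 5 shows why that is not supported: the figure describes deliberate picking between two analyses, needs assumed correlations, and is the same with or without coded arms. Nothing in the documents suggests that such picking is intended.

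The conclusion assumes that the covariates are pre-treatment values, that no unseen document already masks the analyst, and that the analyst can be kept from the allocation records.

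**What to change.** 1. In section {17a}, limit the sentence to clinicians and to staff who allocate or offer treatment, and state that the primary analysis is run on coded arms.
2. Write down in advance the rules for post-randomization exclusions ({11b}) and for the 4-week window. The data manager named in section {19} applies them.
3. The data manager then exports a dataset with arms labelled A/B and without acceptance, refusal or treatment dates. Section {19} already controls access through account authorization, so the analyst's account can be closed to allocation data.
4. The analyst decides on imputation from missingness pooled over both arms and records the decision before any between-arm comparison is run. Coding alone would not be enough without this step.
5. The primary intention-to-treat result is run and locked, and then the code is opened. Per-protocol and CACE analyses follow, since they need refusal data.

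The cost is a few lines of protocol or SAP wording and one coded export. The downside is a two-step analysis. Sample size and recruitment are unaffected. Telephone collection of the primary outcome needs its own remedy.
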